**FIGURE 1 mpr70014-fig-0001:**
[figure not shown]
(A) Drinking diary on the MyDéfi application (in standard alcohol units of 10 g pure ethanol). (B) examples of notifications sent by MyDéfi.

All data is anonymous, not collected for commercial or statistical purposes, and only accessible by the user. All data is encrypted and securely stored using shielding.

Study participants can enter the program with their five numbers inclusion code enabling them to access the version of MyDéfi assigned to them by randomization Ennov Clinical software (“control” or “intervention” group) to start the follow‐up. The email address and password requested are encrypted, inaccessible to investigators, and cannot be used to trace back to an ID. Those data simply allow the user to continue the program if they change phones.

The different versions of the application and the data extracted through MyDéfi are described in Supporting Inforamtion S1 (see “Description of the two versions of the MyDéfi smartphone application”). Examples of the drinking diary and notifications can be found on Figure 1.

#### Micro Blood Sampling: Phosphatidylethanol Measure

2.5.4

The PEth exposure marker will be measured by dried blood spot (DBS) with HemaXis DB 10 kits with 4 self‐samples throughout the study: at the M0, M1, M2 and M3 inclusion visit. After washing hands and cleaning the sampling area on the finger with an alcohol‐free disinfectant wipe, 10 µL of blood is drawn from a channel and then deposited on blotting paper, forming a calibrated blood spot (Figure 2) (Hemaxis 2019). During M0, the investigator provided training in self‐sampling, with a video demonstration. All samplings are labeled with the participant's five number inclusion code and the sample date. Participants are informed during the inclusion visit that only the PEth exposure marker will be quantified in the blood, and that the data will be collected in accordance with French law n.78‐17 of January 6, 1978, and the “European Union Data Protection Directive” (95/46/EC of October 24, 1995).

**FIGURE 2 mpr70014-fig-0002:**
[figure not shown]
HemaXis DB 10 kits instruction for use.

All samples will be analyzed in the Pharmacology and Toxicology laboratory of CHU Amiens‐Picardie according to a validated analytical method (NF EN ISO15189 standard). Dried whole spot of PEth collected on HemaXis DB 10 kits (Ganz, Switzerland) will be determined by a HPLC‐MS/MS (high performance liquid chromatography tandem mass spectrometry) method (8060 LC‐MS/MS, Shimadzu, Marne‐la‐Vallée, France) (Spicher 2022). The analysis method can be found in Supporting Inforamtion S1 (see “Phosphatidylethanol sample analysis method”).

### Outcomes

2.6

Our primary outcome is to demonstrate the effectiveness of a follow‐up with personalized feedback delivered via a mobile application in the intervention group in reducing the number of standard drinks per week compared to the control group by comparing the baseline M0 to the end of follow‐up M3.

Our secondary objectives are to compare between “intervention” group and “control” group a reduction in blood PEth concentration as well as a reduction of alcohol‐related impairments in several psychological dimensions (scores on personality DMQ‐R SF, RCQ, Rosenberg self‐esteem scale, GAD‐7, PHQ‐9) and quality of life questionnaires (AQoLS, BYAACQ, APT Choice) at the baseline M0 and at M3.

### Participant Timeline

2.7

The study schedule can be found on Figure 3 and the entire timeline can be found on Table 2. University students, from the four participating universities, will be proposed to join the SMARTBINGE study via a first email on their institutional email address. In this mail, a link to access the first questionnaires on online LimeSurvey platform will allows them to answer the AUDIT, AUQ, DDQ, Drug Use Questionnaire, UPPS‐S and TCI questionnaires in order to check whether students met the inclusion criteria (presence of BD behavior).

**FIGURE 3 mpr70014-fig-0003:**
[figure not shown]
Study schedule of enrollment and assessments by time points. M0 = Month 0; M1 = Month 1; M2 = Month 2; M3 = Month 3.

**TABLE 2 mpr70014-tbl-0002:** Study schedule of enrollment, assessments, interventions and compensation by time points.

	Initial approach	Inclusion visit (M0)	First follow‐up (M1)	Second follow‐up (M2)	Last follow‐up (M3)
Eligibility screening	X				
Informed consent		X			
Randomization		X			
MyDéfi installation		X			
Self‐questionnaires					
Alcohol consumption					
AUQ	X	X	X	X	X
AUDIT (full scale)	X				
AUDIT‐3R		X	X	X	X
DDQ	X	X			X
Use of other drugs					
Drug use	X	X			X
Fagerström		X			X
CAST		X			X
Personality					
DMQR‐SF		X			X
RCQ		X			X
Rosenberg scale		X			X
TCI‐125	X				X
UPPS‐S	X	X			X
GAD‐7		X			X
PHQ‐9		X			X
Quality of life					
AQoLS		X			X
BYAACQ		X			X
APT/APT choice		X			X
Interventions					
PEth micro‐blood sampling		X	X	X	X
MyDéfi consumption daily diary		X	X	X	X
Compensation					
Gift card		X (20€)	X (20€)		X (60€)

Abbreviations: APT, alcohol purchase task; APT Choice, alcohol purchase task with non‐alcoholic beverage choice; AqoLS, alcohol quality of life scale; AUQ, alcohol urge questionnaire; AUDIT, alcohol use disorders identification test; BYAACQ, brief young adult alcohol consequences questionnaire; CAST, cannabis abuse screening test; DDQ, daily drinking questionnaire; DMQ‐R SF, drinking motives questionnaire revised short form; GAD‐7, generalized anxiety disorder assessment; PHQ‐9, patient health questionnaire; RCQ, readiness to change questionnaire; TCI‐125, temperament and character inventory‐125; UPPS, urgency, premeditation, perseverance, and sensation seeking.

Students meeting the inclusion criteria are contacted again by mail and are invited to the inclusion visit (M0). During the M0 visit, they will sign a consent form and will be randomized into one of the two groups after receiving an anonymous five‐number inclusion code. After downloading MyDéfi application, participants enter their anonymous five‐number inclusion code. This unlocks the version of the application assigned to them during randomization: intervention or placebo application version. Then, the participants will be trained to perform DBS sampling using an HemaXis DB 10 kit with a demonstration video and the guidance of an investigator. After sampling, students answer the M0 online questionnaires on LimeSurvey (see Table 2) at home just after blood sampling, to ensure consistency between the answers to the questionnaires and the blood sample.

During the M1 and the M2 visit, the participants will perform a new micro‐blood sampling using an HemaXis DB 10 kit and answer the AUDIT‐3R and AUQ questionnaires. Finally, for M3 visit, after micro‐blood sampling, participants will answer to the last set of questionnaires online (see Table 2).

### Sample Size

2.8

Based on literature (Gierski et al. 2017), the sample size calculation assumed a standard deviation of 8 weekly number of drinks following Gierski's results on students with BD behavior. The expected outcome in each group drew from two studies: Bertholet's study on students with unhealthy alcohol use and Kaner's meta‐analysis. Bertholet's team anticipated reductions of 2 drinks per week in the intervention group (app users) and 0.39 drinks in the control group (Bertholet et al. 2023). Kaner's meta‐analysis of the comparison between digital versus no or minimal intervention showed a difference of 22.84 g of alcohol per week, thus the goal at M3 is to observe a reduction difference of 2 drinks (Cohen's effect size *d* = 0.25) from the mean number of drinks per week between the two groups (Kaner et al. 2015). Assuming a two‐sided alpha risk of 5% and 80% power, 253 participants per group will be needed. Considering an estimated drop‐out rate of about 20%, a total of 628 participants are necessary for the initial recruitment.

### Data Management and Statistical Analysis

2.9

Participant data will be entered by the investigators into a pseudonymised computer database secured by passwords and centralized at the Amiens University Hospital, to which only the investigators will have access. The database will then be frozen at the end of the study.

For the primary outcome, the reduction in weekly number of drinks will be compared between the two arms using a mixed‐effects analysis of covariance (ANCOVA) model with adjustment for baseline weekly number of drinks and randomization stratification criteria (sex and center). The center will be treated as a random effect.

For the secondary outcomes, the evolution of quality of life, which is collected via questionnaires, will be compared between the two groups using a mixed‐effects ANCOVA model with adjustment for baseline quality of life and randomization stratification criteria (sex and center). The center will be treated as a random effect. Blood PEth concentration will be compared between the two groups using a mixed‐effects ANCOVA model adjusting for initial concentration and stratification factors. Various models will be used to assess the intervention effect throughout the follow‐up period and to check for potential differences in intervention effects across different follow‐up times.

The level of statistical significance chosen for all measures is *p* < 0.05. The software used for data processing will be SPSS. Using a multiple imputation technique, all analyses will be conducted on an intention‐to‐treat basis, including all randomized participants (Full Analysis Set). Intermediate missing data will be handled using maximum likelihood estimation. An analysis based on the Last Observation Carried Forward (LOCF) method will be performed as a sensitivity analysis. We expect a low rate of missing data (< 2%), these methods should be sufficient. In practical term to limit attrition and missing data, we will: compensate participation with 100€ over 3 months (the duration of the study); send reminders by e‐mail to encourage participants to complete questionnaires, consumption diaries and samples on time. Previous studies showing high completion rates (> 90%, e.g. in Bertholet's team work (Bertholet et al. 2023)).

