## Results

3

Since this is a study protocol, we are still in the recruitment phase, which began in March 2024 and will end in March 2026. To date, 116 participants have already been recruited, 39 of whom have completed their follow‐up. These first participants have allowed us to refine our forecast for the attrition rate. Current data show a drop‐out rate of around 10%, that can be attributed to the on‐site visits. This feature increases the power of the study to 85%. The results of the study will be published at a later date.

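### The missing-data plan is called sufficient because under 2% missing data is expected, but the same article plans for about 20% drop-out and reports around 10%

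*Protocol article*

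**What the plan says.** Section 2.9 (Data Management and Statistical Analysis) plans multiple imputation with all randomised participants analysed by intention to treat. For gaps during follow-up it adds: "Intermediate missing data will be handled using maximum likelihood estimation". It names one sensitivity analysis for missing data: "An analysis based on the Last Observation Carried Forward (LOCF) method will be performed as a sensitivity analysis". It then judges the package: "We expect a low rate of missing data (< 2%), these methods should be sufficient". In support it cites earlier studies with completion above 90%.

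Two other sections give different rates of loss. Section 2.8 (Sample Size) states: "Considering an estimated drop‐out rate of about 20%, a total of 628 participants are necessary for the initial recruitment". Section 3 (Results) states: "Current data show a drop‐out rate of around 10%, that can be attributed to the on‐site visits", and raises the power to 85% on that account. The basis for the observed rate is early: "116 participants have already been recruited, 39 of whom have completed their follow‐up".

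**The concern.** The adequacy of the missing-data methods is argued from a rate 5 to 10 times below the rates that the article plans for and observes. Below 2% missing, almost any reasonable method gives the same answer. At 10% to 20% the answer can depend on what is assumed about people with no M3 value.

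Multiple imputation and maximum likelihood, in their usual form, assume that data are missing at random. The outcome here is drinking self-reported through the app under test, so drop-out could plausibly be linked to drinking or to engagement with the app. That link is an assumption; the article does not document it. If it holds, the sensitivity analysis has to show how far the assumption can be wrong before the conclusion changes. LOCF gives one alternative value per person, treats that value as observed, and cannot show this.

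**Working it through.** **Inputs.** From section 2.8: difference 2 drinks per week, SD 8, two-sided alpha 5%, power 80%, 253 per group, drop-out about 20%, total 628. From section 2.9: missing data under 2%, cited completion above 90%. From section 3: drop-out around 10%, power 85%, 116 recruited and 39 completed. Allocation is 1:1, so 314 per arm.

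**1. The plan's own figures.**
- n per group = 2 × (1.960 + 0.842)² × 8² / 2² ≈ 251.2, so 252. The stated 253 agrees to within one.
- 251.2 / 0.8 = 314 per arm, or 628 in total. With 253 per group, 506 / 628 = 0.806, which is 19.4% loss. Either way this matches about 20%.
- Power with loss d uses 314 × (1 − d) per arm, SE = 8 × √(2 / [314(1 − d)]), and power = Φ(2/SE − 1.96).

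| Loss | n per arm | SE | Power |
|---|---|---|---|
| 2% | 307.7 | 0.645 | 87.3% |
| 10% | 282.6 | 0.673 | 84.4% |
| 20% | 251.2 | 0.714 | 80.0% |

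The article's 80% corresponds to 20% loss. Its 85% is close to the value at 10% loss and further from the value at 2%. The power figures therefore count drop-outs as lost to the primary comparison.

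**2. People behind each rate.** 628 × 0.02 = 12.6; 628 × 0.10 = 62.8; 628 × 0.20 = 125.6.

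**3. The cited support.** Completion above 90% means missing data below 10%. It is compatible with 2% but does not imply it.

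**4. Could the observed 10% really be under 2%?** The number of drop-outs is not given, so two counts are assumed. Four drop-outs beside 39 completers (4/43) give an exact 95% interval of about 3% to 22%. Twelve of 116 give about 5% to 17%. Both exclude 2%.

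**5. How much the rate matters.** Suppose the imputed analysis gives a difference of 2 drinks. Let the missing intervention participants in truth drink δ drinks per week more than imputed, with the control arm unchanged. The difference falls by d × δ, and significance is lost when 2 − dδ < 1.96 × SE. Hence δ = (2 − 1.96 × SE) / d.
- 2%: (2 − 1.264) / 0.02 ≈ 37 drinks per week, about 4.6 SD.
- 10%: (2 − 1.319) / 0.10 ≈ 6.8, about 0.85 SD.
- 20%: (2 − 1.399) / 0.20 ≈ 3.0, about 0.38 SD.

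The SE is held at the completers' value, which is a simplification. If intervention drop-outs simply keep none of a 2-drink benefit, the overstatement is 2 × d: 0.04, 0.2 or 0.4 drinks.

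**The case against.** **The low rate may mean something narrower.** Section 2.9 mentions attrition and missing data as separate things, and the under-2% sentence comes shortly after the one on intermediate gaps. It could refer to gaps in retained participants. The diary is also kept on the phone, and section 3 links drop-out to the on-site visits, so someone who stops attending might still record drinks. A reader might therefore go too far in inferring that the three rates are strictly impossible together because every drop-out lacks the M3 outcome; the article does not say whether they do. This part of the objection stands. It does not rescue the sufficiency statement. On the narrow reading that statement omits the larger source of loss, and the restated power treats drop-outs as lost.

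**LOCF is not simply another missing-at-random analysis.** This is correct. For someone who leaves early it carries forward a value near baseline, which resembles no benefit. With equal drop-out in both arms and baseline carried forward, a 2-drink difference becomes 2 × 0.9 = 1.8 or 2 × 0.8 = 1.6, the same reductions as the no-benefit case above. So it would be wrong to say that the plan never departs from missing at random. What remains is that LOCF is one fixed point, with carried values treated as data.

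**Other stronger readings fail.** A reader might infer that LOCF would create a spurious effect through unequal drop-out, but the article reports no drop-out by arm. A reader might also infer that maximum likelihood for intermediate data has no place because the primary comparison uses M0 and M3. Section 2.9 also plans models over the whole follow-up, where it fits.

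**The figure enters no calculation, and a separate analysis plan may add analyses.** Both are fair. They lower the severity, but the article's stated justification is still wrong or undefined.

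**Conclusion.** The concern holds in a limited form. The article rests the adequacy of its missing-data methods on a rate that conflicts with its own planned and observed drop-out, or that, read narrowly, does not cover drop-out. The cited completion rate does not support it.

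In size, the gap is about 13 people against 63 to 126 of 628. The departure needed to overturn a 2-drink result shrinks from about 37 drinks per week to between 6.8 and 3.0. These figures assume SD 8, an estimate of exactly 2 drinks, and a shift in the intervention arm only. Under the same assumptions, losing the whole 2-drink benefit among drop-outs would not by itself remove significance even at 20%, since 2 is below 3.0. The result is therefore not shown to be fragile; the plan gives no way to show that it is robust.

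The sample size and power statements are sound, and the primary model is not at fault. Severity: should be fixed.

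**What to change.** - In section 2.9, restate the expected proportion of missing M3 outcomes as 10% to 20%, or define the under-2% figure as intermittent gaps in retained participants only. Make it agree with sections 2.8 and 3.
- Delete the statement that the methods should be sufficient.
- Name a sensitivity analysis that varies the missing-data assumption: delta-adjusted multiple imputation reported as a tipping point, or reference-based multiple imputation. It can replace LOCF or stand beside it.
- Keep the primary ANCOVA with multiple imputation. A switch to a repeated-measures primary model is not needed to cure this defect.

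The cost is some extra programming and a less favourable stated rate. Recruitment, visits and procedures do not change. Recruitment is planned to March 2026, so the change should be recorded before unblinding.

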## Results

3

Since this is a study protocol, we are still in the recruitment phase, which began in March 2024 and will end in March 2026. To date, 116 participants have already been recruited, 39 of whom have completed their follow‐up. These first participants have allowed us to refine our forecast for the attrition rate. Current data show a drop‐out rate of around 10%, that can be attributed to the on‐site visits. This feature increases the power of the study to 85%. The results of the study will be published at a later date.

## Discussion

4

Binge drinking is prevalent among university students. In general, student populations do not seek medical help. New technological tools to facilitate dematerialized and anonymous access are a necessity in terms of public health to reach this vulnerable population. The main purpose of the SMARTBINGE study, a prospective, randomized, double‐blind, multi‐center clinical trial is to demonstrate the efficacy of personalized feedback delivered via the MyDéfi mobile application in reducing the number of standard drinks per week in the “intervention” group of young adult students presenting a BD behavior.

To limit BD dangerous practice, a number of studies have tested the effect of mobile e‐health applications via smartphone use, which is widespread among this vulnerable population. Nevertheless, a number of biases have been identified in previous clinical studies studying mobile applications. Williamson's team's systematic review of the literature raised the issue of the lack of evidence supporting the hypothesis of the effectiveness of personalized notifications on drinking behavior, pointing to a number of pitfalls (Williamson et al. 2022). Yet this type of BI is preferred by users (Perski et al. 2018) and therefore potentially more effective. The authors highlight the fact that the randomized double‐blind studies, under‐represented in the literature, are interested in the impact of an app in general, and not the additional impact of personalized notifications included in an app, advising that each e‐BI should be isolated from a digital placebo effect (Torous and Firth 2016a). Indeed, in most studies on the effect of an application, the “control” group uses either the usual treatment (Gustafson et al. 2014), or a web page containing normative information (Bertholet et al. 2023; Gonzalez and Dulin 2015; Oldham et al. 2024), or nothing at all (Bertholet et al. 2015). The importance of a good “control” group is crucial, and while the examples cited can be used to determine the effect of an application, they cannot be used to determine the additional effects discussed above. Our study rectified this shortcoming by comparing two versions of the same mobile application in two separate randomized double‐blind arms: the effect of a “treatment" (intervention) diary mobile application with personalized feedback versus a “placebo" (control) diary mobile application with generic feedback.

Another limitation of studies using a consumption diary pointed out by Williamson's team (Williamson et al. 2022) lies in the subject's self‐reported consumption, overcome by measuring Peth in this study. Our secondary objectives are to seek a reduction of PEth whole blood concentration. As far as we know, this protocol is the first to correlate application mobile use with an objective measurement of last month's alcohol consumption, although blood PEth concentrations have already been correlated with BD practices, self‐reported (Chen et al. 2023; McLaughlin et al. 2022) or measured via the AUDIT score (Piano et al. 2015). The concentration of PEth in whole blood will be determined using a sensitive (LOQ = 9 ng/mL) and reproducible HPLC‐MS/MS method, with a simple preparation technique, equivalent to recently published HPLC‐MS/MS techniques (Kechagias et al. 2015; Nalesso et al. 2011; Zheng et al. 2011), fully validated in accordance with international guidelines (European Medicines Agency (EMA), 2015; “Scientific Working Group for Forensic Toxicology (SWGTOX) Standard Practices for Method Validation in Forensic Toxicology,” 2013). Furthermore, the in vitro instability of this molecule is resolved by using a DBS sampling device on blotting paper, allowing non‐invasive self‐sampling, and therefore not requiring medical staff, facilitating transport and extending the storage time of samples (Faller et al. 2013; Kummer et al. 2016).

Finally, these longitudinal studies are subject to the phenomenon of attrition, which we are trying to limit by proposing compensation for participants from M0 to M3. The 3‐month duration is typical for this type of study (ranging from 2 weeks to 1 year) (Williamson et al. 2022). However, it will be necessary to study the effect of MyDéfi over the long term (beyond 3 months).

Taking into account the recommendations and limitations of previous clinical studies, the design of our study sought to limit the numerous biases usually found in this type of study, by a single mobile application with two versions with a real placebo application (a “placebo” version with a diary with generic feedback vs. a “intervention" version with a diary with personalized feedback) while correlating the declarative consumption results with an objective biomarker and a measure of the many potential beneficial effects associated with a reduction in BD. If our study confirms the hypothesis that a e‐BI with personalized feedback reduces alcohol consumption, the MyDéfi mobile application specializing in BD could be recommended to provide ongoing, tailor‐made interventions combined with the advantages of e‐health, close to students' requirements (Buscemi et al. 2010; Kapitány‐Fövény et al. 2022), reaching this vulnerable population.

